#### Updated increased sample size

When recruitment of the proposed sample size (*N* = 384) was complete, attrition and completeness of data were considered to assess the appropriateness of the sample size. Completion rates for T2, T3, and T4 varied between 74% and 84%, which was lower than the anticipated 90%. To account for this increased attrition, an increased sample size was required. The additional participant calculation is based on the following: If 70% of the sample completes at least 2 postpartum timepoints, a sample of 346/0.70 = 495 is needed; this is 111 more than planned. Thus, an increased proposed sample size of *N* = 495 is needed to account for potential impacts of attrition.

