## Statistical methods

### Statistical methods for primary and secondary outcomes {27a}, {27b} and {27c}

A detailed descriptive profile will be created for all outcomes, intervention conditions, sample characteristics, and intervention adherence. Descriptive statistics will be as follows: (1) For continuous variables that are approximately normally distributed without outliers: mean and standard deviation; (2) for continuous variables that are not normally distributed or have outliers: median and interquartile range; and (3) for discrete variables: frequency and percentage.

We will report the frequency and percent of participants who completed each timepoint and who have missing data at each timepoint. Adverse event frequency and type will be reported with frequencies and percentages. We will compare the proportion of withdrawn or missing participants at each timepoint and the proportion of adverse events by condition using chi-squared tests.

#### Effectiveness for Aim 1

To test aim 1, which is ISI (primary) and SRI (secondary) will be lower in the Healthy Sleep Program than the Control condition, we will use regression analyses. Analyses will be intention to treat, with participants analysed in the condition to which they were assigned regardless of actual intervention receipt. Significance is set at *α* = 0.01, two-tailed. We will calculate the expected raw difference in outcomes between treatment and control with 95% confidence intervals, along with the standardised difference to measure the effect size. All effectiveness analyses for Aim 1 will be conducted in R.

The dual primary (ISI at pregnancy and postpartum) and two secondary (SRI at pregnancy and postpartum) outcomes will be used as described previously (see “Outcomes {16}”) with the outcomes treated as continuous variables. Analyses will be separate regressions for each outcome, with the outcome as the dependent variable. Treatment condition will be dummy coded (Healthy Sleep Program = 1, sleep hygiene education = 0) and included as the focal predictor. The outcome measure at baseline (T1) will be included as a covariate. That is, ISI at T1 will be included for both ISI primary outcomes, and the SRI at T1 will be included for both SRI secondary outcomes. Randomisation strata will be fully crossed and dummy coded, and these dummy codes will be included as covariates [61]. The method selected for statistical inference for the main analyses will depend on features of the data.

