If outcome data are missing, we will use multiple imputation through chained equations (MICE, [63]) based on predictive mean matching (PMM; [64]). We will generate 100 imputed datasets.

*Second*, if model residuals are approximately normally distributed, we will use normal theory-based standard errors to calculate confidence intervals and *p*-values. If model residuals are not normally distributed, we will use a nonparametric bootstrap with percentile-based confidence intervals based on 20,000 bootstrap samples. In this case, in addition to reporting 95% confidence intervals, we will use the 99% bootstrap percentile intervals to determine statistical significance based on whether or not the interval includes 0. The distribution of model residuals will be determined by fitting a linear regression model and creating a density plot of the residuals and a Q-Q plot of the observed residuals against a normal distribution.

*Third*, if there are no outliers in the model residuals, we will use regular linear regression. If there are outliers in the model residuals, we will use quantile regression and use a median (50th percentile) estimator. Outliers in the residuals will be determined by fitting a linear regression model, extracting the residuals and creating a density and rug plot.

The above choices will be combined as necessary based on the data. For example, if outcome data are missing, the residuals demonstrate non-normality and there are outliers, we would use quantile regression, non-parametric bootstrapping and multiple imputation. In cases where we use both bootstrapping and multiple imputation, we will use the approach of bootstrapping in the outer loop and then using imputation in the inner loop [65]. That is, for each of 20,000 bootstrap samples, we will use MICE with PMM to generate a single imputed dataset with added noise reflecting the uncertainty of the imputation, resulting in a total of 20,000 datasets that are both bootstrapped and imputed. This was selected as a simulation study demonstrated that while it is computationally demanding, it provides the best validity [65].

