We will conduct and report sensitivity analyses. *First*, we will conduct a complier average causal effect analysis, which estimates the impact of an intervention in the population subgroup that complies with its assigned treatment, which will illuminate the intervention effect on women who received the minimum recommended amount of intervention. *Second*, we will conduct controlled multiple imputation, with an offset, δ, added to the imputed missing outcome data [66]. Specifically, we will vary *δ* assuming that participants who dropout and have missing data experience worse-than-expected outcomes. That is, a non-random pattern whereby people are more likely to dropout or have a missing outcome when the outcome is worse. We will vary the magnitude of *δ* and report treatment estimates across the range of *δ* values.

We will conduct two secondary analyses. First, we will test a condition × recruitment source interaction to assess intervention effect heterogeneity across sources. Second, we will conduct linear mixed models for ISI and SRI using scores at each individual timepoint to compare trajectories of insomnia and daytime symptoms between conditions. Protocol deviations will be documented, and sensitivity analyses will be carried out, if necessary, to examine whether findings hold with or without participants with deviations.

#### Economic evaluation for Aim 2

Cost-effectiveness and cost-utility analyses will be conducted from a societal perspective, summarising the health and productivity effects of the intervention during the trial period. Usual care is selected as the comparator to directly inform treatment and funding decisions. Direct costs of the active control condition will be excluded from analyses, with estimates of treatment effects for primary and secondary outcomes interpreted as conservative relative to usual care.

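### The missing-not-at-random analysis makes no provision for δ to differ by arm, so with similar missingness it is a weak test of arm-specific informative dropout

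*Protocol article*

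**What the plan says.** The relevant text is in the protocol article under Statistical methods for primary and secondary outcomes, in the part on effectiveness for Aim 1. The main analysis imputes missing outcomes by chained equations with predictive mean matching. The second sensitivity analysis departs from missing at random: "we will conduct controlled multiple imputation, with an offset, δ, added to the imputed missing outcome data". The direction is fixed for everyone alike: "we will vary *δ* assuming that participants who dropout and have missing data experience worse-than-expected outcomes". The output is described as follows: "We will vary the magnitude of *δ* and report treatment estimates across the range of *δ* values". Treatment condition is not mentioned in this description. There is one symbol, one range, and one mechanism, namely that people with worse outcomes are more likely to be missing.

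Three other statements bear on it. The same section plans a comparison of missingness between arms: "We will compare the proportion of withdrawn or missing participants at each timepoint and the proportion of adverse events by condition using chi-squared tests". The significance level is given as "Significance is set at *α* = 0.01, two-tailed". The section Updated increased sample size reports completion of 74% to 84% at T2 to T4 and replans on the supposition "If 70% of the sample completes at least 2 postpartum timepoints". The section Protocol and statistical analysis plan {5} says that the analysis plan is contained in this manuscript.

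**The concern.** A δ analysis should show how far the missing outcomes would have to depart from the imputation model before the conclusion changes. For a comparison between arms, the departure that matters most is one that differs by arm. Here such a difference is plausible. HSP participants get a 60-minute session, further consultations and six timed deliveries of material, and are contacted repeatedly if they do not book or attend. Control participants get one booklet. Participants cannot be blinded, and the ISI is self-reported. Reasons for not responding may therefore differ between arms even where the rates are the same.

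If δ is the same in both arms, most of its effect on the estimate is subtracted out when the missing fractions are close. The reported range of estimates would then look stable, and readers could take this as evidence against a scenario that the analysis hardly probes. If control has more missing data, a penalty meant to be pessimistic would increase the apparent benefit.

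**Working it through.** **Inputs from the protocol article.** Target effect d = 0.40 (f² = 0.04); α = 0.01 two-tailed; 85% power; 18 coefficients; 346 analysed; planned N = 384, revised to 495; completion 74% to 84% at T2 to T4 (16% to 26% missing, pooled over arms); planning figure of 70% for the postpartum endpoint (30% missing).

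**Assumptions, not in the documents.** ISI SD of 5, so d = 0.40 is 2.0 points; the missing fractions per arm; the sizes of δ; δ added at the level of the endpoint.

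**The plan's own figures.** The noncentral F calculation with one numerator degree of freedom gives v = 327.5 denominator degrees of freedom. Adding 18 gives 346 analysed. Then 346/0.90 = 384.4 and 346/0.70 = 494.3, in agreement with 384 and 495. The sample size is not in question here.

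**Shift in the treatment estimate.** Let p be the missing fraction in each arm. In a linear mean model, adding δ to the imputed values raises each arm's mean by δ × p, so

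shift = δ_HSP × p_HSP − δ_C × p_C, and for a common δ, shift = δ × (p_HSP − p_C).

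Lower ISI is better, so a positive shift takes benefit away.

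- Common δ = 3, 30%/30% missing: 3 × (0.30 − 0.30) = 0.
- δ = 3 in HSP only, 30% missing: 3 × 0.30 = 0.9 points, and 0.9/2.0 = 45% of the target effect.
- Common δ = 3, 35% HSP and 25% control: 3 × 0.10 = 0.3 points.
- Common δ = 3, 25% HSP and 35% control: 3 × (−0.10) = −0.3 points, in favour of HSP.
- δ = 3 in HSP only at 16% to 26% missing (the T2 to T4 range): 3 × 0.16 = 0.48 to 3 × 0.26 = 0.78 points.

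**Standard error under a common δ.** The outcome SD grows by about √(1 + p(1 − p)δ²), with δ in SD units. For δ = 3/5 = 0.6 and p = 0.30 this is √(1 + 0.21 × 0.36) = 1.04, about 4%. At δ = 1 SD it is √1.21 = 1.10.

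**Where significance is lost, HSP only, 30% missing.** With SE = 2/√346 = 0.1075 SD, the smallest significant effect at α = 0.01 is 0.279 SD. An effect of 0.40 loses significance at δ = (0.40 − 0.279)/0.30 ≈ 0.40 SD and reaches zero at 0.40/0.30 = 1.33 SD. This SE ignores the gain from baseline adjustment. With the simulated SE of 0.095 the threshold is 2.576 × 0.095 = 0.245, and significance is lost at (0.40 − 0.245)/0.30 ≈ 0.5 SD.

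**Simulation check.** N = 495, true effect −0.40 SD, baseline correlation 0.5, normal-model imputation with 20 imputations, 400 replicates:

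| Missing HSP/control | δ HSP, δ control (SD) | Mean estimate | SE | Significant at 0.01 |
|---|---|---|---|---|
| 30%/30% | 0, 0 | −0.406 | 0.094 | 97% |
| 30%/30% | 0.5, 0.5 | −0.405 | 0.096 | 97% |
| 30%/30% | 1, 1 | −0.395 | 0.103 | 89% |
| 35%/25% | 1, 1 | −0.306 | 0.103 | 67% |
| 40%/20% | 1, 1 | −0.198 | 0.104 | 25% |
| 30%/30% | 0.5, 0 | −0.249 | 0.095 | 52% |
| 30%/30% | 1, 0 | −0.098 | 0.098 | 5% |

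The simulated estimates follow the formula.

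**The case against.** A reader might infer that the plan prescribes one common offset, that this offset cancels between arms, and that the analysis therefore cannot test informative dropout. The documents do not support that.

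First, the text is silent on arms. A common δ is the natural reading of a single symbol applied to all participants with missing data, but it remains an inference. The method is also cited to a source that is not at hand. It can be said that an article leaves the layout of a δ grid to a fuller document. That defence is weakened because the article says it contains the analysis plan, and because the mechanism it describes does not refer to condition.

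Second, cancellation is exact only with equal missing fractions and a mean model. With unequal fractions a common δ does move the result: at 40%/20% and 1 SD it halves the effect. Even with equal fractions the standard error grows and some significance is lost. No missing fractions by arm are given, and the plan intends to compare them, so equality is not presumed. That comparison can reveal unequal rates. It cannot reveal dropout that is informative to different degrees at equal rates.

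Third, the plan allows median regression if residuals have outliers, and the shift formula does not carry over exactly to that estimator.

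Fourth, 30% missing is a planning supposition, and completion at T2 to T4 was better than that. The plan's own mechanism, worse outcomes leading to missingness, is coherent. Calling an arm-specific version the only real threat would be a matter of judgement.

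All four points limit the claim. None shows that the plan provides for an arm-specific departure.

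**Conclusion.** The point holds in a limited form. The planned δ analysis does not provide for offsets that differ by arm. Under the natural reading and the linear model, it moves the treatment estimate only through the difference in missing fractions. It is therefore a weak test, not an empty one, of informative dropout that differs between arms, and it favours HSP if control loses more participants.

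The size depends on assumed values. With an SD of 5 and 30% missing in each arm, 3 points applied in HSP only costs 0.9 of 2.0 points, against about nothing for the same common offset. An HSP-only departure of roughly 0.4 to 0.5 SD would be enough to lose significance for an effect of 0.40 SD. With less missing data the shift is smaller in proportion.

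This concerns the robustness statement attached to the primary result. The primary analysis and the sample size are unaffected. The change is worth making because it is nearly free.

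**What to change.** State in the sensitivity analysis that δ_HSP and δ_control vary separately over a grid in ISI points. Include the case of HSP only with δ_control = 0, and keep the common-δ runs as the diagonal. For each primary endpoint, report the estimate and interval over the grid and the tipping point at which the test is no longer significant at α = 0.01, or say that it is not reached. A grid that runs to at least 5 points would cover the loss of significance in the illustration above. If median regression is selected, run the same grid with that estimator and do not rely on the closed-form shift. Show the missing fractions by arm beside the results.

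Fix the grid before any outcome analysis. The statisticians are not blinded to condition (Who will be blinded {24a}), and data collection is still under way (Trial status), so this can still be done.

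The cost is a few extra runs of code already planned and a sentence or two of text. The downside is that the robustness statement may turn out less favourable.

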### Methods for additional analyses {27d}

Exploratory aims may be conducted via longitudinal analyses such as mixed effects models; latent growth models will be used to explore changes in outcomes over time, as well as predictors of change trajectories. Models such as cross-lagged panel analyses will be used to explore associations of constructs over time.

### Interim analyses {28b}

No interim analyses were planned, and no formal stopping rules are specified given the low risk of behavioural intervention used in this study, and that the benefits are unlikely to be overwhelmingly strong to warrant early termination of the trial.

### Protocol and statistical analysis plan {5}

The protocol and statistical analysis plan are included in the present manuscript.

## Oversight and monitoring

### Composition of the coordinating centre and trial steering committee {3d}

The steering committee will include the chief investigator, trial statistician, study coordinator, and site leads. Additionally, the study is also informed by the Community Reference Group which involves individuals with lived experience who provided insight prior to study commencement and will meet at least three times throughout the study. The study will be centrally coordinated from the Monash University site, with both Monash Health and the Royal Women’s Hospital sites having a site lead overseeing site-specific activities. The research team overseeing study operations (e.g. recruitment and intervention delivery) will meet weekly to assess progress. The investigators for the project will meet every 4 to 6 months to oversee the progress of the trial.

### Composition of the data monitoring committee and its role and reporting structure {28a}

The trial will be overseen by a DSMB which is responsible for the stewardship of the trial over all participating sites or institutions. The stewardship will include continuous review of participant recruitment, accrual, retention, and withdrawal. It further involves oversight of participant management, adherence to protocol-specified regimens, and procedures for data management and quality control. The DSMB will involve a minimum of four independent (i.e. not directly involved in trial) experts in the areas of obstetrics and sleep health. The DSMB will be responsible for safeguarding the interests of trial participants by assessing the safety of the interventions during the trial and the general progress of the trial. All DSMB members will be independent of the funder.

### Frequency and procedures for monitoring trial conduct {29}

The trial will be overseen by DSMB. The DSMB will be presented with a report of data completeness, ongoing recruitment status (e.g. target recruits, participants recruited, timeliness) and intervention adherence. The DSMB will meet at least three times during the trial, with the chair of DSMB to call ad hoc meetings as needed.

### Protocol amendments {31}

If protocol amendments are required, these amendments will be submitted to the primary ethics committee (Monash Health Human Research Ethics) and communicated to all other ethics committees following approval. If these amendments will impact existing participants, these participants will be contacted via email or phone. Protocol amendments will be reported in publications.

## Dissemination policy {8}

Irrespective of study outcomes, results of the study will be disseminated through publication of peer-reviewed journal articles and through conference presentations. Results of the study may also contribute to theses of research students. Participants will be sent a summary of the study outcome about 18 months after the completion of the study. If shown clinically effective and cost-effective, the research team plans to work with clinical partners to implement the intervention in community perinatal care. Authorship for dissemination publications will be decided by the International Committee of Medical Journal Editors’ Authorship guidelines.

## Discussion

This project will provide needed empirical data on the effectiveness, cost-effectiveness and implementation potential of a cognitive behavioural therapy for insomnia in the perinatal period. Importantly, this study will inform potential future implementation of CBT-I for perinatal insomnia symptoms in community care by identifying barriers and enablers to sustainable implementation of a scalable CBT-I program for perinatal populations. Additionally, through the implementation assessment, this study will identify ways in which (i.e. through midwives, hospitals, general practitioners (GP) clinics) at-risk perinatal individuals may be identified and targeted for treatment.

The results of the wider implementation of this intervention may improve future sleep health and mental health outcomes for individuals during the perinatal period, thus reducing the excessive burden of health care providers and improving outcomes for individuals and families.

## Trial status

Protocol Version 5, dated 29 September 2025. Participant recruitment began on 09/02/2023, with the first participant enrolled on 20/02/2023. Recruitment closed after protocol submission (07/10/2024) on 01/12/2024, with the final participant enrolled on 08/11/2024. The trial data collection is ongoing with the last planned follow-up to be conducted on approximately 01/03/2027.

## Data Availability

After completion of the study, no more than 7 years after publication, data will be de-identified and made publicly available through Monash bridges (or a similar data repository). Statistical analysis code will be published via journal publications or public code sharing repositories (e.g. GitHub).

## Abbreviations

ARDES: Attention-Related Driving Errors Scale
AQoL-4D: Assessment of Quality of Life
AUD: Australian Dollar
BISQ: Brief Infant Sleep Questionnaire
BSD: Big Stick Design
CAT: Computer Adaptive Testing
CBT-I: Cognitive Behavioural Therapy for Insomnia
CD: Chen’s Design
CEQ: Credibility Expectancy Questionnaire
COM-B: Capability, Opportunity, and Motivation - Behaviour
DBAS-16: Dysfunctional Beliefs and Attitudes Scale
DSMB: Data Safety Management Board
EAT-8: Eating Attitude Test Short Form
EBCD: Efron’s Biased Coin Design
FIRST: Ford Insomnia Response to Stress Test
GLM: Generalized Linear Models
GP: General Practitioner
IPAQ-SF: International Physical Activity Questionnaire-Short Form
IQI: Infant Quality of Life Instrument
ISI: Insomnia Severity Index
MICE: Multiple Imputation through Chained Equations
MP: Maximal Procedure
MTI: Maximally Tolerated Imbalance
PBR: Permuted Block Randomisation
PICF: Participant Information and Consent Form
PMM: Predictive Mean Matching
PRISM: Practical Robust Implementation and Sustainability Model
PROMIS: Patient Reported Outcomes Measurement Information System
PROPr: Patient Reported Outcomes Measurement Information System — Preference
QALY: Quality-Adjusted Life Years
RCT: Randomised Controlled Trial
REDCap: Research Electronic Data Capture
RMEQ: Reduced Morningness-Eveningness Questionnaire
RPBR: Random Permuted Block Randomisation
SAE: Serious Adverse Events
SHINE: Sleep Health in Perinatal Care
SRI: Sleep-Related Impairment
TDF: Theoretical Domains Framework
USDA: United States Department of Agriculture
WPAI: Work and Productivity and Activity Impairment
